Optimizing Ankle-Foot Orthotic Prescription Using an Emulation Test‐Drive Strategy

Funding Agency: Department of Defense - CDRMP

Version 3; 07/20/2023

Abstract

Provide a summary of the study (recommended length: less than 500 words).

Ankle foot orthoses (AFOs) are often necessary to overcome mobility limitations related to lower limb neuromusculoskeletal injury. While the availability of AFOs for improving function is expanding, options remain limited and especially relative to ankle-foot prostheses. There is a critical need to better optimize AFO designs and provide evidence-based tools to guide their prescription. The proposed study utilizes an exoskeleton capable of emulating AFOs by modulating the magnitude and/or timing of torque.

We aim to (1) test the ability of the AFO emulator to reproduce the user experience of wearing commercially available (‘actual’) AFOs during different in-lab activities (walking, running, stair climbing; level ground, ramps) in individuals with lower limb musculoskeletal injury. This aim will determine if the proposed AFO emulator framework can provide an option for quickly exploring multiple devices in a short period of time. We aim to (2) test the ability of a short-term, in-laboratory evaluation of function, mobility, and preference with the AFO emulator to predict those same outcomes longer-term (i.e., after 2 week use in the community) in AFO users with lower limb musculoskeletal injury. This aim will determine the predictive ability of a brief test-drive strategy using emulated AFOs to identify function, mobility, satisfaction, and preference at followup after two weeks of use in the community environment with corresponding actual AFOs. We aim to (3) allow the user to self-tune AFO emulator stiffness settings while walking and compare function, mobility, preference to the clinically prescribed AFO. This aim will determine if an AFO test drive strategy can be used to better optimize user satisfaction and patient reported outcomes relative to the current standard of care.

We will recruit up to 56 individuals with lower limb musculoskeletal trauma who are currently using an AFO. Participants will first undergo a short-term assessment of three emulated and actual AFOs over two in-lab sessions. Subsequently, participants will complete a community trial with the actual AFOs (2 weeks each). Patient reported outcomes, including user preference, an activities trial, and performance tests (for the actual AFOs only) will be recorded at each assessment. Patient reported outcomes and activities trial will also be recorded for the user self-tuned emulator session.

List of Abbreviations

2MWT - Two-Minute Walk Test

ABC - Activity Balance Confidence Scale

AFO - Ankle Foot Orthosis

AIC - Akaike Information Criterion

CDMRP – Congressionally Directed Medical Research Programs

CITI - Collaborative Institutional Training Initiative

CLiMB - Center for Limb Loss and MoBility

CS - Compound Symmetric

CRADA - Cooperative Research and Development Agreement

DoD - Department of Defense

EACE - Extremity Trauma and Amputation Center of Excellence

ESR - Energy Storing and Returning

FSST - Four square step test

HIPAA - Health Insurance Portability and Accountability Act

HJF - Henry Jackson Foundation

HRPO - Human Research Protection Office

HSD - Honest Significant Difference

ID - Identification

IDEO - Intrepid Dynamic Exoskeletal Orthosis

IRB - Institutional Review Board

LME - Linear Mixed Effect

NCOPE - National Commission on Orthotic and Prosthetic Education

NBWT - Narrowing Walking Beam Test

O&P - Orthotics and Prosthetics

OIF - Operation Iraqi Freedom

OND - Operation New Dawn

OEF - Operation Enduring Freedom

OPUS - Orthotics and Prosthetics Users’ Survey

PHI - Protected Health Information

PI - Principal Investigator

PII - Personally Identifiable Information

PROMIS - Patient-Reported Outcomes Measurement Information System

QUEST - Quebec User Evaluation of Satisfaction with Assistive Technology

RPE - Rating of Perceived Exertion

SAE - Serious Adverse Event

SIBCR – Seattle Institute for Biomedical and Clinical Research

TUG - Timed Up and Go

U-SAE - Unexpected Serious Adverse Event

USAMRMC - U.S. Army Medical Research and Materiel Command

VA - Department of Veterans Affairs

VAPSHCS - VA Puget Sound Health Care System

VHA - Veterans Health Administration

WRNMMC - Walter Reed National Military Medical Center

Contents

[Protocol Title: 7](#_Toc338328603)

[1.0 Study Personnel 7](#_Toc338328604)

# Introduction

**Burden of injury.**

Over 17,200 U.S. Service members have been medically evacuated from theater due to battle or musculoskeletal-related injuries sustained during Operations Iraqi Freedom (OIF), New Dawn (OND), and Enduring Freedom (OEF) [1]. Global military figures show that the largest burden of injury from the global war on terrorism is extremity trauma [2], which represents 64% of the $170-million projected disability benefit costs and causes the largest percentage of days on limited duty [3]. Nearly 50% of all extremity injuries involve the lower extremities [4], thus impacting mobility, community participation, and the overall quality of life of affected individuals. With the advancement of forward medical care on the battlefield, there is a corresponding increase in Service members surviving with these major lower extremity traumatic injuries which previously would have resulted in amputation. The military has a vested interest in maximizing injured Service member function and quality of life across the continuum of care. The relatively young mean age of these Service members implies higher vocational and recreational demands and expectations.

**Ankle-foot orthoses (AFOs).**

AFOs are often necessary to overcome mobility limitations related to lower limb neuromusculoskeletal injury. The availability of orthotic options for improving function is expanding, but still limited [5]. Relative to the field of prosthetics, orthotics research and development has remained relatively understudied and underfunded for decades. Moreover, outcomes are better for individuals who have sustained lower limb amputation than for those who have had their limb salvaged or reconstructed [6], which is potentially due to specialized technology available and provided to those with amputation, and not to those with limb salvage [6]. To date, a wealth of information on comparative effectiveness of designs, standardization of certain outcome measures, and surveys exist to identify the needs and preferences of prosthesis users, but the same level of scientific evidence does not exist for AFO users. The current evidence is insufficient to develop Clinical Practice Guidelines. Despite the lack of scientific evidence, Medicare expenditures for orthotics in 2016 reached $1 billion [7]. A 2015 National Commission on Orthotic and Prosthetic Education (NCOPE) study projected that by the year 2025, the number of certified orthotists will need to increase by 90% to meet future patient demands [8]. There is a critical need to better optimize orthotic devices for patients and provide evidence-based tools for clinicians. The proposed study with its unique test-drive strategy will address these unmet needs by optimizing the process of selecting an AFO in a patient-centered and patient-specific manner.

**Limitations of available information to guide AFO prescription.**

The scarcity of publicly available objective orthotic mechanical property (e.g., stiffness) data and different vendor stiffness naming paradigms (e.g., numbered 1-7, arbitrary units of measurement, color names) limits clinicians’ ability to choose an AFO that optimally matches a given patient’s needs. It is a constant challenge to compare devices across vendors to hone in on the ideal design features for a given patient.

The interaction between the user and the AFO is largely determined by its mechanical properties that can impact the degree to which movement is either restricted or augmented. One key AFO design mechanical property is stiffness. The stiffness of the device about the ankle impacts the extent to which the device offers energy storage and push-off enhancement during waking. For example, a stiffer device offers less range of motion but may provide greater support and higher rates of energy storage and return, which may be desirable for someone wishing to engage in higher impact activities. There is evidence to support that an optimal match exists between an individual’s gait-related impairments and AFO ankle stiffness [9]. There is also an optimal stiffness at which energy expenditure during walking can be reduced [10-13]. Thus, optimizing AFO stiffness is an important aspect of optimally restoring mobility and participation in activities of daily living in individuals with lower limb deficits resulting from musculoskeletal trauma. However, there is limited evidence to guide this process. Quantitative stiffness data, for example, are only available for select devices in the research literature, often only comparing a few devices, many of which are custom fabricated orthoses. A recent review paper by Totah et al. [14] summarized stiffness values about the ankle joint from a range of devices, often having to estimate values from data provided. This lack of objective mechanical properties data and lack of standardization underscores the need for a test-drive strategy for AFO prescription.

**Current prescription process.**

Optimal AFO prescription should align the needs and abilities of the patient with the functional characteristics of the device but, once again, evidence is limited. Currently, the AFO prescription process relies on clinician intuition, training, experience, and qualitative guides provided by vendors. Clinical evaluation for AFO prescription is typically based on patient’s physical examination (e.g. muscle strength and joint ranges of motion), functional evaluation, medical history, body mass, and overall mobility goals. The clinician then selects from the commercially available devices, of which there are a number of makes and models of varying materials, designs, and componentry. For instance, mechanical joints can permit range of motion while stops can be incorporated to limit motion. AFOs may incorporate a variety of materials in design: thermoplastics, composites such as fiberglass or carbon fiber and resin, metals, and leather. Each material, and the way in which it is integrated into the device, imparts different mechanical properties. AFOs may be prefabricated and available off the- shelf or custom molded to the patient. Custom carbon fiber dynamic AFOs are now being used more frequently. These designs have been developed to offer energy-storing-and returning (ESR) properties and are commonly intended for patients who desire to participate in high impact activities. However, matching the right device with the patient can be challenging. Moreover, to reduce expense and time, clinicians are typically tasked with getting it right on the first try. This is a significant limitation in clinical care to which our proposed test-drive strategy (described below) will address.

**AFO user input in the prescription process.**

Successful patient adoption of an AFO device relies on patient satisfaction and perceived mobility, thus there is substantial benefit to incorporating patient feedback into the AFO prescription process. Moreover, patients using lower limb assistive technology routinely want and expect their input to be considered in their plan of care [15, 16]. Involving the patient in the clinical decision making process has been shown to improve functional outcomes [17]. However, there are limited opportunities for patients to try out different devices and offer feedback, particularly on custom-made AFOs. Trial and error of numerous devices (particularly for custom devices) would be inefficient, expensive, and highly labor-intensive. Therefore, patients are unable to explore the range of options the way they would be able to with footwear in a shoe store. In a shoe store, a customer may try any number of shoes within a given category (walking or running, for example) that may meet his or her needs. An AFO user’s only experiential comparison is often between the new selected device and not having any prior device or between the new device and a previous device that the patient had identified as not well-suited for his or her needs.

Numerous comparative effectiveness studies have sought to identify the best device for a patient. However, the post-hoc tests are generally only capable of identifying the better device between two. Determining which AFO provides optimal patient outcomes is a challenging task. There is no singular optimization criterion that will work for all patients. Thus, we propose a test-drive strategy for different AFO devices focused on improving satisfaction, function and mobility. This novel strategy has great potential to streamline the prescription process, enable the patient to provide experiential feedback, and improve outcomes.

**Test-drive strategies.**

To address the limitations in the current prescription process, we have developed a commercially available, customizable robotic exoskeleton emulator (Caplex system, Humotech, Pittsburgh, PA) that is worn around the ankle joint. The system includes the off-board control system and actuator unit, the ankle-foot exoskeletal end effector (worn by the user), shoes that can be quickly swapped with the device, and the flexible tether. The exoskeleton is actuated and controlled by offboard actuator unit and control hardware. Thus, this setup delivers an ultra-powerful exoskeleton end-effector with minimum worn mass and inertia. The wearable component only weighs 1.4 kg (including the mass of an athletic shoe). The exoskeleton is capable of emulating active or passive device conditions by applying torque based on time or ankle angle, depending on different applications. Benchtop experiments have demonstrated the emulator’s exceptionally high torque control performance [18-20]. An impedance control law can be used to mimic the elastic behavior. This system has successfully been used to emulate a broad range of passive, spring-like properties [20], making it well suited for applications with passive-dynamic AFOs. Thus, the system can be programmed to emulate the behavior of a broad array of commercially available (*actual*) AFOs without requiring the user to physically change devices. This provides the wearer with the experience of swapping out different design features in real time via software interface without the costly and time-intensive trial and error process of comparing *actual* devices. The emulator is not meant to replace clinical expertise but to augment the tools currently available to better optimize the design and prescription of AFOs.

# Objectives

The overarching goal of this research is to optimize mobility, function and satisfaction for Service members, Veteran, and civilian AFO users with lower limb musculoskeletal injuries. To achieve this, our primary purpose is to determine the extent to which a ‘test-drive’ strategy, using an AFO emulator, can be used to predict device function, mobility and preference outcomes with corresponding commercially available (*actual*) AFOs in Service members and Veterans with lower limb musculoskeletal trauma.

**Specific Aim 1**: Test the ability of the AFO emulator to reproduce the user experience of wearing *actual* AFOs during different in-lab activities (walking, running, stair climbing; level ground, ramps) in individuals with lower limb musculoskeletal injury. This aim will determine if the proposed AFO emulator framework can provide an option for quickly exploring multiple devices in a short period of time.

**Research Question 1a**: Do self-reported measures of preference differ between *emulated* and corresponding *actual* AFO conditions?

**Hypothesis 1a**: Preference scores for *emulated* AFO conditions will be strongly correlated with preference for the corresponding *actual* AFO.

**Research Question 1b**: Do measures of performance and self-reported outcomes differ between *emulated* and *actual* AFOs conditions?

**Hypothesis 1b**: Measures of performance and self-reported outcomes in the *emulated* AFO condition will be strongly correlated with those using corresponding *actual* AFOs.

**Specific Aim 2*:*** Test the ability of a short-term, in-laboratory evaluation of function, mobility, and preference to predict those same outcomes longer-term (i.e., after 2 week use in the community) in AFO users with lower limb musculoskeletal injury. This aim will determine the predictive ability of a brief test-drive strategy using *actual* and *emulated* AFOs to identify function, mobility, satisfaction, and preference at follow-up after two weeks of use in the community environment with corresponding *actual* AFOs.

**Research Question 2a**: Do measures of user preferences identified during a brief test-drive session with an *emulated* AFO predict user preferences after the *actual* AFO is worn longer-term in the community environment?

**Hypothesis 2a**: Initial preference scores for each *emulated* AFO will be strongly correlated with preference for the corresponding *actual* AFO at follow-up.

**Research Question 2b**: Do measures of user preferences identified during a brief test-drive session with an *actual* AFO predict user preferences after the same *actual* AFO is worn longer-term in the community environment?

**Hypothesis 2b**: Initial preference scores for each *actual* AFO be strongly correlated with preference at follow-up.

**Research Question 2c**: Do measures of user preferences identified during a brief test-drive session correlate with performance measures and self-reported measures of mobility after the same *actual* AFO is worn longer-term in the community environment?

**Hypothesis 2c**: Initial *emulated* preference scores be strongly correlated with performance-based and self-reported mobility measures at follow-up.

**Research Question 2d**: Do measures of user preferences identified during a trial with the *actual* AFO correlate with performance measures and self-reported measures of mobility after the same AFO is worn longer-term in the community environment?

**Hypothesis 2d**: Initial *a*ctual preference scores be strongly correlated with performance-based and self-reported mobility measures at follow-up.

**Exploratory Aim:** Allow the user to self-tune AFO emulator stiffness settings while walking (***patient-optimized***) and compare function, mobility, preference to the clinically prescribed AFO (***clinician-optimized***). This aim will determine if an AFO test drive strategy can be used to better optimize user satisfaction and patient reported outcomes relative to the current standard of care.

**Research Question 3a**: How does preference differ between the patient-optimized setting on the AFO emulator and in the clinically-prescribed *actual* AFO?

**Hypothesis 3a**: Preference scores for the user-optimized setting on the emulator will be greater than those in the clinically prescribed AFO.

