# Study Procedures

## 4.1 Study Design

This is a clinical trial with a participant-blinded, cross-over study design with repeated-measures assessments will take place at each site. Short-term, in-lab sessions will be used to address Aim 1 (i.e., comparing in-lab *emulator* trials to in-lab corresponding *actual* AFO trials) and the Exploratory Aim (comparing in-lab patient-optimized emulator trials to in-lab prescribed *actual* AFO trials). Aim 2 will compare short-term in-lab trials with longer-term follow-up using corresponding *actual* AFOs. We will assess user preference, satisfaction, perceived mobility and performance in *emulated* and *actual* AFOs to determine whether the emulator and/or a brief trial of *actual* AFOs can predict user mobility and AFO preference following longer term use in the community environment.

See section 5.5 below for data collection procedures.

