## 4.6 Data Analysis

**Aim 1.** The purpose of Aim 1 is to test the ability of the AFO emulator to reproduce the user experience of wearing actual AFOs during different activities (walking, running, stair climbing; level ground, ramps) in individuals with lower limb musculoskeletal injury. We will consider the outcome measures as continuous response variables in the statistical analysis. We will evaluate the data from the in-lab actual and in-lab *emulated* sessions using a linear mixed effect (LME) regression with the *emulated* AFO data as the independent fixed effect, the *actual* AFO data as the dependent fixed effect, and subject participant as a random intercept.

**Hypothesis 1A**. In Specific Aim 1A, we are testing the hypothesis that the experimental AFO preference measured during the in-lab *emulated* session will be significantly correlated with the experimental AFO preference measured during the in-lab *actual* session. This model estimates a change in *actual* AFO preference per unit change of *emulated* AFO preference.

**Hypothesis 1B**. In Specific Aim 1B, we are testing the hypothesis that self-reported measures and biomechanics will be significantly correlated between the in-lab *emulated* session and the in-lab *actual* session. This model operates the same as in 1A, substituting measures of function and mobility for preference.

**Aim 2.** The goal of Aim 2 is to determine if the in-lab (*emulated* and *actual*) measurements are a good predictor of the longer-term measurements made following a take home trial. To perform this analysis, we compute a similar LME regression as Aim 1 with the *emulated* *or actual* in-lab AFO data as the independent fixed effect, the *actual* take-home trial AFO data as the dependent fixed effect and subject participant as a random intercept.

**Hypothesis 2A**. In Specific Aim 2A, we are testing the hypothesis that the experimental AFO preference measured during the in-lab *emulated* session will be significantly correlated with the experimental AFO preference measured during the take home-trials. This model operates the same as in 1A, substituting measures of take-home trial preference as the dependent variable.

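### Aim 1 asks whether emulated and actual AFO scores differ, but section 4.6 tests only a slope, which a constant gap between the platforms leaves unchanged

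*Protocol*

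**What the plan says.** The Objectives state Aim 1 as an agreement-type goal: "Test the ability of the AFO emulator to reproduce the user experience of wearing" the actual devices. Both research questions under it are about a difference. RQ1a asks "Do self-reported measures of preference differ between" the two conditions, and RQ1b asks "Do measures of performance and self-reported outcomes differ between" them. Section 4.1 also describes a comparison: "Short-term, in-lab sessions will be used to address Aim 1 (i.e., comparing in-lab" emulator trials with the matching actual-AFO trials.

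The hypotheses under these questions are about association. Under Hypothesis 1a, emulated preference "will be strongly correlated with preference for the corresponding" actual AFO.

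Section 4.6 follows the hypotheses. Aim 1 is analysed "using a linear mixed effect (LME) regression with the" emulated score as predictor, the actual score as outcome and a random intercept per participant. For 1A the estimand is a slope: "This model estimates a change in" the actual score for each one-unit step in the emulated score. The claim tested is that emulated preference "will be significantly correlated with the experimental AFO preference measured during the in-lab" actual session. The power paragraph counts rejections of a zero slope.

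For Aim 1 the protocol states no mean difference, no agreement measure and no reading of the intercept. The only comparison of means in section 4.6 is the paired t-test of the Exploratory Aim.

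**The concern.** The protocol asks one question and plans the analysis of another. It is not simply loose wording, because the other aims keep the ideas apart. RQ2a and 2b ask about prediction and RQ2c and 2d about correlation, and regression suits them. RQ3a asks about a difference and gets a comparison of means. Only RQ1a and 1b ask about a difference and get none.

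Two things are at stake. First, two stated research questions would have no planned answer. Second, the Exploratory Aim compares preference on the emulator directly with preference in the prescribed actual AFO. Any general like or dislike of the emulator as a platform enters that contrast and could create or hide a result. The introduction describes a tethered device with a worn mass of 1.4 kg, so some offset is plausible, though the protocol gives no data on it. Aim 1 is where such an offset could be measured.

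**Working it through.** **Inputs from the protocol.** 10-point preference scale, primary outcome (4.5). Three AFOs, each tried on both platforms (4.5). N = 50 in the power simulation and 56 recruited, with 12% dropout (4.6). Null hypothesis: slope = 0 (4.6).

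**The plan's own figure.** Power is stated as 97% (preference) and 98% (mobility). It cannot be reproduced, because the pilot slope and residual error are not given as numbers. The point does not depend on it.

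**Step 1: algebra.** The planned model is

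actual = b0 + b1 × emulated + participant effect + error.

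Add a constant c to every emulated score. The same fit becomes

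actual = (b0 - b1 × c) + b1 × (emulated + c) + participant effect + error.

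Only the intercept moves. The slope, its standard error, its p-value and the correlation stay as they were.

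**Step 2: numerical check.** One data set was simulated with 50 participants, three AFOs and continuous scores without floor or ceiling (illustrative SDs). It was fitted with the planned model, then refitted after shifting all emulated scores.

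| Shift in emulated scores | Slope (SE) | p | r | Intercept | Mean emulated minus actual |
|---|---|---|---|---|---|
| 0 | 0.740 (0.059) | 6.9e-36 | 0.737 | 1.39 | +0.13 |
| -2 | 0.740 (0.059) | 6.9e-36 | 0.737 | 2.87 | -1.87 |
| +2 | 0.740 (0.059) | 6.9e-36 | 0.737 | -0.09 | +2.13 |

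The intercepts agree with step 1: 1.39 + 0.740 × 2 = 2.87 and 1.39 - 0.740 × 2 = -0.09. Halving every emulated score also left the test statistic at z = 12.51.

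**Step 3: can the intercept stand in for the difference?** In the fitted model the mean actual-minus-emulated difference is b0 + (b1 - 1) × mean emulated score. It equals the intercept only if the slope is 1. The gap can be worked out from the data, but the intercept as printed is not the gap.

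**Step 4: what a difference analysis would deliver.** The protocol gives no SD for paired differences, so 1.5 to 2.5 points is assumed, with one rating per AFO and platform.

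- If all 50 × 3 = 150 differences are independent, the half-width is 1.96 × SD / √150: 0.24 (SD 1.5), 0.32 (SD 2.0), 0.40 (SD 2.5).
- If differences are fully clustered within 50 people, it is 2.01 × SD / √50: 0.43, 0.57, 0.71.
- Using one mean difference per participant, power to detect a 2-point gap (two-sided 5%, assumed) is above 99.9% at SD 2, 99.6% at SD 3 and 93.4% at SD 4.

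**Step 5: would a ±1-point equivalence test be safe?** Take SD 2.5, fully clustered. The standard error is 2.5 / √50 = 0.354, and the 90% half-width is about 1.68 × 0.354 = 0.59. The observed difference must then lie within 1 - 0.59 = 0.41. With a true difference of zero, power is 2Φ(0.41 / 0.354) - 1, about 75%.

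**Step 6: which outcomes exist on both platforms?** Section 4.5 has participants do the Activities Trial and the same questionnaires in both in-lab sessions, and gait biomechanics are recorded during that trial. The performance tests are added in the actual-AFO session only, and the abstract says the same. No emulated performance-test score will exist. Hypothesis 1B in section 4.6 already names only self-report and biomechanics, while RQ1b and Hypothesis 1b in the Objectives still name performance.

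**The case against.** The strongest defence is that the analysis fits what the trial is for. The Objectives give prediction as the primary purpose, and Aim 1's stated use is to explore several devices quickly. An offset common to all three emulated AFOs leaves their order unchanged and so does no harm there. Hypotheses 1a and 1b are correlation hypotheses, and the regression tests association. This stands. A reader might infer that the slope analysis is wrong and should be replaced, but the documents do not support that.

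A reader might also infer that a gap would be lost for good. It would not. Both sets of scores are collected and the gap can be computed, and descriptive means may well be in an SAP that is not shown. What the protocol lacks is a planned estimate or interpretation that answers its own question. That mismatch lies within the protocol, because section 4.6 already fixes model, estimand and null hypothesis.

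Nor does the protocol say that a non-zero slope will be reported as reproduction of the actual device. Section 4.6 promises only a significant correlation. The risk comes from setting that result beside the wording of Aim 1.

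Two limits on the remedy also stand. A compulsory equivalence margin is debatable: it could fail a useful test-drive tool over a harmless common offset, and its power is modest at the upper assumed SD. Limits of agreement would be wide, about ±2.9 to ±4.9 points (1.96 × 1.5 to 1.96 × 2.5). No repeat in-lab session of the same condition is planned, so they could not be separated from ordinary retest noise.

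**Conclusion.** The concern holds in a limited form. RQ1a and RQ1b ask about a difference and Aim 1 about reproduction, yet section 4.6 tests only a slope against zero. On a continuous scale, a uniform gap of any size, 2 points included, gives exactly the same Aim 1 test result as no gap. On the bounded 10-point scale this is exact only if no rating meets the floor or ceiling. The planned data could settle the question with a 95% half-width of roughly 0.24 to 0.71 points. That range rests on assumed SDs of 1.5 to 2.5, one rating per AFO and platform, and 50 completers.

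The slope analysis remains valid for Hypotheses 1a and 1b, and Aim 2's predictive analyses are unaffected. The performance-test part of RQ1b cannot be answered by any analysis, because those tests are not done on the emulator. The change is worth making but is not fatal to the trial.

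**What to change.** In section 4.6, for 1A and 1B, keep the slope model and add a mixed model of score on platform (emulated or actual), AFO and session order, with a participant random effect. Report the emulated-minus-actual difference with a 95% CI. Apply it to preference and to the self-report and biomechanical measures collected on both platforms. Limits of agreement may be shown descriptively for preference. Do not make an equivalence margin a condition of success unless the sponsor justifies one.

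State that in-lab performance tests are done with actual AFOs only, and reword RQ1b and Hypothesis 1b accordingly.

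If the sponsor prefers not to add a difference analysis, reword Aim 1, RQ1a and RQ1b as association. Under either option, do not conclude from a non-zero slope alone that the emulator reproduces the actual device.

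The cost is one extra model per shared outcome, on data already planned, with no added visits or participants.
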